#### Measurement of spatial gait parameters

The spatial gait parameters of the participants in both groups will be recorded using the footprint method as described by previous publications [55–57]. Footprints provide a simple and economical method from which step length, stride length, foot angle and stride width can be measured. While sitting on the chair, a pair of flat shoes (slippers) will be given to the participant to wear. Different sizes will be provided to the participants to suit their foot size. All the shoes will be provided with a strap that will be tied to the affected heel to avoid missing steps during the gait training. Ink paste will be applied at the bottom of the participant’s shoes. They will be then asked to stand and walk with the instruction “walk as you normally do” across the 10-m path (as described in the procedure for overground walking training) and footprint sequences from the ground surface will be recorded. The participants will be asked to look directly forward during walking as observing the footprints could alter their gait patterns. At least six footprints will be obtained. The first few steps of the gait footprints will be disregarded because they may not be indicating the stable gait of the participants. Spatial gait parameters will be measured from the footprints using a measuring tape for each of the selected gait components. Each participant will perform three trials of walking and the spatial gait parameters will be recorded in each trial; the average will be then computed. The measurements will be recorded to the nearest centimeters for both the loaded paretic lower limb and non-loaded paretic lower limb during the overground training (Fig. 3). All the parameters will be measured and recorded separately for each leg. The ground floor will be cleaned and mopped to be cleared for the next participant. The spatial gait parameters and symmetry to be measured are fully described in Table 2.

**Fig. 3 Fig3:**
[figure not shown]
Measurement of stride length (distance AB), step length (distance CD), step width (distance EC) and stride width (FG)

#### Measurement of temporal gait parameters

Similar to the measurement for the spatial gait parameters and symmetry, each participant will perform three trials of walking and the temporal gait parameters (gait speed and cadence) will be recorded in each trial; the average will be then computed. Measurements will be carried out in seconds using a stopwatch each for the loaded paretic lower limb and non-loaded paretic lower limb during the overground training (Table 2).

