### Randomisation and blinding

Upon completion of all the baseline assessments, consenting participants will be stratified by MRS scores (i.e. 1, 2 and 3) and randomised into two groups; overground walking with paretic lower limb loading or overground walking without paretic lower limb loading in a 1:1 ratio (Fig. 2) by a third party not involved in other aspects of the study. Allocation of participants will be concealed using consecutive numbered, sealed and opaque envelopes prepared using a web-based randomisation tool (available at https://www.sealedenvelope.com) with permuted block size of 6. All outcome assessors will be blinded to participants’ group allocation. However, it will be impossible to blind physiotherapists and participants considering the nature of the study interventions.

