The procedure for the overground walking with lower limb loading is similar to that described by Abba et al. [48] except for the addition of weight to the paretic lower limb and increase in intensity of walking in the current study. The walking will be conducted on a flat surface of 15 × 10 m dimensions in the physiotherapy gymnasium. Participants will undergo to and fro overground walk with a 1.5-kg sandbag attached to the paretic limb. The 1.5-kg sandbag was chosen based on the findings of our pilot study (unpublished data) conducted on 18 chronic stroke survivors. We found this weight to be the most comfortable and tolerable weight for overground walking among stroke patients who presented with mild to moderate disability based on the scores of the MRS. Prior to the overground walking, participants will be asked to sit in a relaxed position on a chair with their feet on the ground. The selected weight will be strapped 2 cm above the ankle of the paretic lower limb with the malleoli being the reference point [43]. The strapping will be done in such a way that it is not loose or too tight to give discomfort to the participants while carrying out the training. Afterwards, the participants will be instructed to stand and then walk to and fro a 10-m path (within 15 × 10 m dimensions) labeled with adhesive tape to guide the walking in a straight line. Each participant will be instructed to walk with standardised instruction “walk at your normal, comfortable pace” [49] for 5 min after which they will be asked to stop and rest for 2 min. The training will be repeated 3 times in the first 2 weeks of the study (15 min), 4 times in weeks 3–4 of the study (20 min), and 5 times in weeks 5–8 of the study (25 min). Weight will be unloaded from the paretic limb after completing the training session. The participants will be monitored throughout as they carry out the training, and those reporting symptoms of exertional intolerance outside the target zone (i.e. 12–14) on Borg’s rate of perceived exertion (RPE) scale [50] would be terminated at any time. Treatment will be delivered individually, thrice weekly for 8 weeks. The duration of the training session is expected to last from 40 min in the first week to 50 min in the 8th week. Details of the duration and progression of the study interventions are provided in Table 1.

**Table 1 Tab1:** Duration and progression of the study interventions

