### Outcome assessments and follow-ups

The primary outcomes will be step length and gait speed whereas the secondary outcomes will be step length symmetry ratio, stride length, stride length symmetry ratio, stride width, cadence and motor function (Table 2). All outcomes will be assessed at baseline prior to randomisation, 4, 8 and 20 weeks after the start of intervention. All participants will be reminded about thier follow-ups via phone call on regular basis.

**Table 2 Tab2:** Description of primary and secondary outcomes and time points of assessments

S/N	Outcome measure	Description/administration	Psychometrics	Assessment point

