	**Primary outcomes**			
1	Step length	It will be measured as the distance from the heel strike of one foot to the heel strike on the next successive step of the opposite foot, using the midpoint of the heel square as the reference point (distance CD measured in cm) See Fig. 3	The measure is easy and has adequate test–retest reliability (*r* = 0.97) [50] and concurrent validity with strobe-light photography [51]	Baseline 4th week 8th week 20th week
2	Gait speed	It will be measured as the distance covered in meters per time taken in seconds to walk a specified distance on a level surface. In this study, it will be calculated as the ratio of 10 m distance per unit time covered during the gait training	The measure has excellent test–retest reliability (ICC = 0.94–0.99) [49, 52] and concurrent validity (*r* = 0.95) with GAITRite system [53]	Baseline 4th week 8th week 20th week

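### The protocol contradicts itself on whether the gait outcomes, both primary ones included, are measured with or without the ankle weight; if it is worn at weeks 4 and 8, those comparisons are confounded and the assessors unblinded

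*Protocol article*

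**What the plan says.** Three places in the protocol article tie gait measurement to training.

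- *Measurement of temporal gait parameters* (gait speed, cadence): timed "using a stopwatch each for the loaded paretic lower limb and non-loaded paretic lower limb during the overground training".
- *Measurement of spatial gait parameters* (which covers step length, the other primary outcome): recorded "for both the loaded paretic lower limb and non-loaded paretic lower limb during the overground training".
- *Table 2*, gait speed row: "it will be calculated as the ratio of 10 m distance per unit time covered during the gait training". This row does not mention load.

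For the loading arm, the intervention section says "Participants will undergo to and fro overground walk with a 1.5-kg sandbag attached to the paretic limb" and "The selected weight will be strapped 2 cm above the ankle of the paretic lower limb", with removal once the session is finished. The control arm has the same programme without the weight.

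Two other statements bear on the point. *Randomisation and blinding*: "All outcome assessors will be blinded to participants’ group allocation". *Outcome assessments and follow-ups*: "All outcomes will be assessed at baseline prior to randomisation, 4, 8 and 20 weeks after the start of intervention".

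**The concern.** The trial asks whether eight weeks of training with a loaded limb improves gait more than the same training without load. That calls for both arms to be measured under the same condition. If the measurement sections are followed to the letter, participants in one arm could be timed and footprinted with 1.5 kg above the ankle and those in the other arm without it.

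Two things would then be at stake. The between-group difference at the affected visits would no longer isolate the training effect. And anyone timing or recording the walk would see the allocation. Assessor blinding is the only blinding the trial has, since the protocol says that participants and physiotherapists cannot be blinded. The gait outcomes are taken by hand, with stopwatch and tape measure, so it matters here.

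**Working it through.** **Step 1. Compare the passages.**

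| Point | Text suggesting measurement during training | Text suggesting a separate walk |
|---|---|---|
| When | Both measurement sections and the gait speed row refer to training | Baseline precedes randomisation; week 20 is 20 − 8 = 12 weeks after training ends |
| Who | Not stated in those sections | Two therapists with no part in screening or treatment assess outcomes, blinded |
| How | Loaded and non-loaded limb named | Slippers, ink, three averaged trials, an instruction different from the training one, no step for strapping on the weight |
| Weight off? | Removed after the session | Not stated for assessment |

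The left column cannot apply at baseline or week 20. It can apply only at weeks 4 and 8. The two columns cannot both be right, and no sentence decides between them.

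**Step 2. What follows if the weight is worn at weeks 4 and 8.** *Statistical analysis* specifies a mixed model with time, treatment and their interaction, baseline as reference. Let τ be the training effect at a visit and δ the immediate effect of wearing the weight. The between-group contrasts in change from baseline are:

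- week 4: τ₄ + δ
- week 8: τ₈ + δ
- week 20: τ₂₀

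No term in the model separates δ from τ. The shift from week 8 to week 20 is τ₂₀ − τ₈ − δ, so taking the weight off would look like a gain or loss of effect at follow-up.

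**Step 3. Illustrative size.** No figure in the protocol is disputed. Its total of 42 is reproduced by the within-between F-test with f = 0.20, ρ = 0.5 and three measurements: λ = 0.20² × 42 × 3 / (1 − 0.5) = 10.08 on 2 and 80 degrees of freedom, power 0.803. The number of measurements is my inference; the text does not give it. From 42, n = 21 per arm.

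Assume no training effect and compare one visit with baseline, two-sided α = 0.05. In outcome SDs:

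- change score: SD = √(2(1 − 0.5)) = 1, standard error = √(2/21) = 0.309
- baseline-adjusted: SD = √(1 − 0.5²) = 0.866, standard error = 0.866 × 0.309 = 0.267

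Chance of a significant difference = P(Z > 1.96 − δ/SE) + P(Z < −1.96 − δ/SE):

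| δ (assumed, SD) | Change score | Baseline-adjusted |
|---|---|---|
| 0 | 5% | 5% |
| 0.1 | 6.2% | 6.6% |
| 0.2 | 9.9% | 11.6% |
| 0.3 | 16.3% | 20.2% |
| 0.5 | 36.7% | 46.5% |

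For δ = 0.2, change score: 0.2/0.309 = 0.65, and P(Z > 1.31) + P(Z < −2.61) ≈ 0.099.

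**The case against.** The strongest reply is that this is loose drafting. The footprint section describes a walk that is not the training walk: it has its own footwear, instruction and number of trials, and no strapping step. The authors also use the word training loosely. The same section explains the slipper strap by reference to gait training, although the slippers are introduced only for the inked assessment. The loaded and non-loaded wording may be shorthand for the two groups, or may mean that each participant is measured both ways. Neither section assigns load by arm, and the gait speed and step length rows of Table 2 do not mention load at all.

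Much of this stands. A reader might infer that the plan is to measure the loading arm with the weight on and the control arm without it, and that the assessors are therefore unblinded. The documents do not establish that. The visits without training and the separate assessors support a drafting slip at least as well.

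It does not remove the problem. The wording appears in both gait measurement sections, is echoed in the outcome table, and concerns both primary outcomes. It is a positive statement, not a detail that a journal article has merely left out. If participants are measured both ways, the text does not say which value enters the model. The protocol also accepts that therapists at its two centres may differ slightly in how they assess, so contradictory text can be followed in different ways.

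The arithmetic has limits too: δ is assumed, and a single-visit comparison is not the planned four-visit model.

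**Conclusion.** The measurement condition for the gait outcomes is contradictory as written and must be reconciled. Confounding and unblinding are conditional on the weight being worn at assessment.

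If it is worn at weeks 4 and 8, the between-group contrasts at those visits shift by the full immediate effect of the weight, week 20 does not, and assessors can see the allocation for both primary outcomes. The direction is unknown: the shift could imitate a benefit or hide one. The range of about 10% to 47% for δ between 0.2 and 0.5 SD rests on an assumed δ, zero training effect, ρ = 0.5 and 21 per arm. It shows how sensitive the comparison would be and is not an estimate of actual bias. The Motricity Index is not described as measured under load, so the contradiction concerns the gait outcomes.

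**What to change.** Reconcile *Randomisation and blinding*, *Outcome assessments and follow-ups*, Table 2 (gait speed) and the two gait measurement sections. Delete the references to training and the loaded/non-loaded wording from the measurement text. Replace them with one statement: at baseline and weeks 4, 8 and 20, all gait outcomes are measured in both arms with no weight on the limb, in an assessment walk separate from the training session, by the blinded assessors. Assessing before any training that day, with the treating therapist absent, would be an optional safeguard.

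Recruitment began in November 2021 and was expected to finish in February 2023, the month of publication, so many assessments may already have been made. If any participants are known to have been measured with the weight on, flag those records for a sensitivity analysis.

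The cost is rewording and scheduling, with no change to the sample size. The drawback is that weight status may not be recoverable for past visits.

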#### Measurement of motor function

Lower limb motor function of the participants will be assessed using the Motricity Index. Description on how the motor function will be measured is fully provided in Table 2.

#### Adverse events

Adverse events of therapeutic exercise are well known due to their wide application in the healthcare sector. Expected non-serious adverse events related to exercise interventions may include fatigue, falls, muscle soreness or cramps, dizziness and excessive blood pressure responses. Expected serious adverse events include transient ischemic attack (TIA), recurrent stroke, myocardial infarction and sudden death. Based on the findings of our pilot study (unpublished data), no adverse events were reported. However, all participants in this trial will be informed during recruitment of the possibility of experiencing serious and non-serious adverse events. The physiotherapists responsible for treatment will closely monitor the patients during the overground walking training. Adverse events will be reported immediately to the trial management committee which is identical to the authors of this protocol in addition to a physician for prompt action. Adverse events will be also reported to the research ethics committee of Kano State Ministry of Health, Nigeria.

### Sample size calculation

The sample size for this study was estimated using the following parameters: F-test, mixed between-within subjects analysis of variance (ANOVA); alpha (*α*) level of 0.05 (5% chance of drawing a false positive conclusion or committing type I error); power of 0.80 (80% probability of avoiding false negative conclusion; effect size of 0.20 (small effect size was used as no similar RCT could be found); and correlation among repeated measures of 0.5. Based on these assumptions, the total sample size required is 42. However, while accounting for 15% (*n* = 6) dropout rate, a minimum sample size of 48 participants (24 per group) will be finally required. The sample size calculation was performed with G-Power software version 3.1.9.2 for Windows [58]. 

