### Statistical analysis

Descriptive statistics of mean, standard deviation, percentage and frequency will be used to summarise the data. Comparison of baseline categorical variables among groups will be conducted using Fisher’s exact test or chi-square test and for continuous variables using independent *t*-test or Mann–Whitney *U* test where applicable. Intention-to-treat principle will be used for the primary statistical analysis by including each participant’s available data in accordance with original allocation and irrespective of the level of attendance. The primary and secondary outcomes will be analysed using linear mixed-effects models (LMMs) by including time (4, 8 and 20 weeks, baseline will be the reference), treatment (overground walking with paretic lower limb loading and overground walking without paretic lower limb loading) and a time × treatment interaction as fixed effects, and a random intercept to account for within-subject correlations. Treatment effect will be defined as the adjusted between-group difference and the associated 95% confidence intervals (CI). We opted to use LMMs because it provides unbiased estimates when data are missing at random [59]. Additionally, per-protocol analysis using the LMMs will be performed as sensitivity analysis by excluding randomised participants who did not received allocated intervention, or who attended fewer than 18 treatment sessions, received proscribed concomitant intervention known to influence gait, and experienced exclusionary medical conditions listed in the study exclusion criteria. All the statistical procedures will be performed using SPSS version 23.0 (IBM Co., Armonk, NY, USA) at a probability level of 0.05.

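### The stated 5% false-positive chance is a per-test rate: two primary outcomes at three visits are judged at 0.05 with no primary visit, leg or success rule

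*Protocol article*

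**What the plan says.** All references are to the Protocol article.

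- *Outcome assessments and follow-ups* names two primary outcomes of equal rank: "The primary outcomes will be step length and gait speed". The schedule is: "All outcomes will be assessed at baseline prior to randomisation, 4, 8 and 20 weeks after the start of intervention". No visit is called primary.
- *Measurement of spatial gait parameters*: "All the parameters will be measured and recorded separately for each leg". Table 2 defines step length without saying which leg's value is the primary outcome.
- *Statistical analysis* specifies a linear mixed model with fixed effects for time, treatment and their interaction, "including time (4, 8 and 20 weeks, baseline will be the reference", and a random intercept. The effect of interest is given as: "Treatment effect will be defined as the adjusted between-group difference and the associated 95% confidence intervals (CI". Neither a visit nor a leg is attached to it. The level is set for everything: "All the statistical procedures will be performed using SPSS version 23.0 (IBM Co., Armonk, NY, USA) at a probability level of 0.05".
- *Sample size calculation* uses one F-test from a mixed between-within ANOVA, with alpha 0.05, power 0.80, effect size 0.20 and correlation 0.5. It glosses the alpha as a "5% chance of drawing a false positive conclusion or committing type I error".
- The aim at the end of *Background* hypothesises superiority on step length and gait speed, without saying whether one or both must be shown.

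**The concern.** A 5% chance of a false-positive conclusion is true of one test. Here the primary question can be answered by either of two outcomes, each with three post-baseline contrasts, and step length exists once per leg. Nothing in the article prevents the choice of outcome, visit or leg from being made after the data are seen. In a trial of 48 participants, one chance result could then be reported as superiority of loading.

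The article does more than leave multiplicity to a later document. It fixes 0.05 for all procedures and states what error rate this buys. If the answer is that both outcomes must succeed, the error statement can be rescued, but the 80% power was calculated for a single test and not for the joint requirement.

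**Working it through.** **1. The plan's own figure.** Inputs from *Sample size calculation*: f = 0.20, correlation ρ = 0.5, two groups, alpha 0.05, power 0.80, N = 42. For the group × time interaction with m measurements, λ = f²·N·m/(1−ρ), df1 = m−1, df2 = (N−2)(m−1).

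- m = 3: λ = 0.04 × 42 × 3/0.5 = 10.08, df 2 and 80, power 0.803. N = 42 is reproduced.
- m = 4 (the number of planned assessments): λ = 0.04 × 42 × 4/0.5 = 13.44, df 3 and 120, power 0.871.

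The calculation covers one test of one outcome at 0.05. The difference between 3 and 4 measurements is a separate matter; it enters here only through the per-outcome power.

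**2. Correlation between visit contrasts.** In a random-intercept model the change-from-baseline contrasts at two visits have covariance proportional to 1−ρ and variance proportional to 2(1−ρ). Their correlation is therefore 0.5 whatever ρ is. The correlation between outcomes is not given in the article, so it is varied from 0 to 0.9 as an assumption.

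**3. Chance of at least one false positive, either outcome sufficing.** Two-sided tests at 0.05. Independent tests give 1 − 0.95^k: 9.8% for k = 2, 26.5% for k = 6, 37.0% for k = 9. Correlated normal statistics (1,000,000 draws, visit correlation 0.5) give:

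| Correlation between outcomes | One test per outcome (2) | Each visit tested (2 × 3 = 6) | Each visit, both legs (3 × 3 = 9) |
|---|---|---|---|
| 0 | 9.8% | 23.5% | 33.0% |
| 0.3 | 9.5% | 22.9% | 31.8% |
| 0.5 | 9.1% | 21.9% | 29.4% |
| 0.7 | 8.4% | 20.3% | 25.8% |
| 0.9 | 7.0% | 17.2% | 20.2% |

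- Using the omnibus interaction F-test as the single test per outcome (24 per arm, 4 visits) gives 10.0%, 9.4% and 8.3% at outcome correlations 0, 0.5 and 0.8.
- With both legs counted but one test each, the rate is about 8 to 14%.
- If the visit contrasts were correlated 0.9 rather than 0.5, six tests would give about 12 to 16%, still above 5%.

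**4. Direction.** Counting only results that favour loading roughly halves each figure: about 3.5 to 5% for two tests, 9 to 12% for six and 10 to 18% for nine. The nominal value for one two-sided test is 2.5%.

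**5. If both outcomes must succeed.** With one test each, error is at most 5%. If any visit may count for each outcome, error can reach 12.5%, the three-visit rate for one outcome. Joint power from a bivariate normal, with correlation 0 to 0.8 between the test statistics:

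- Each outcome at 80%: 0.80² = 0.640, rising to 0.729.
- Each outcome at 87.1%: 0.871² = 0.759, rising to 0.818.

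**6. Detectable week-8 difference under Holm.** 21 per arm, ρ = 0.5, 80% power. Difference = (z for two-sided alpha + 0.842) × SD × √(2/21), where √(2/21) = 0.309. The second figure in each range uses the t distribution with 40 df.

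| Contrast | SD factor | alpha 0.05 | alpha 0.025 (first Holm step) |
|---|---|---|---|
| Baseline-adjusted | √(1−0.25) = 0.866 | 0.75–0.77 SD | 0.82–0.85 SD |
| Change from baseline | √(2 × 0.5) = 1 | 0.86–0.89 SD | 0.95–0.98 SD |

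**The case against.** **The article never says that each visit will be tested separately.** The sample size rests on one F-test and the model contains one interaction per outcome. A reader might infer that the true error rate is 20 to 30% or more. The documents do not support that: it requires every visit to be tested, any single result in either direction to count as success, and assumed correlations. With one test per outcome the figure is 7 to 10%. This objection stands against the high figure, not against the point. An omnibus test does not yield the between-group difference and confidence interval by which the treatment effect is defined, so visit contrasts must enter somewhere, and none is singled out.

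**Recording each leg separately is data collection, and the symmetry ratios need it.** That is correct. A reader might infer that both legs' step lengths are primary tests, but no section says so. The nine-test figure is an upper bound. What remains is that the leg defining a primary outcome is not named.

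**The hypothesis joins the two outcomes with a conjunction, so both may be required.** This is possible, and with one test each it would control error. It is not stated as a success rule. Nor does it follow that power would then be badly short: the loss is clear if each outcome has exactly 80%, but at the 87% that the stated inputs give with four assessments, joint power lies around 80%.

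**Multiplicity procedures often sit in an analysis plan, and the 5% phrase is a textbook gloss.** This is fair for the detail, and it lowers the severity. It does not remove the point, because the article fixes 0.05 for all procedures and states the resulting error.

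**Conclusion.** The point holds in a bounded form. The 5% describes a single test, and under every rule examined in which either outcome suffices, the trial-wide error exceeds it. The size depends on a rule the article does not state: about 7 to 10% with one test per outcome, about 17 to 23% with three visits each, and up to about 33% if both legs also count. These are two-sided rates, assuming visit contrasts correlated 0.5 (as the planned model implies) and outcomes correlated 0 to 0.9. If both outcomes must succeed on one test each, error is controlled and the cost is power, by an amount that depends on the per-outcome power. The defect is an unspecified decision rule beside a definite error statement, not a demonstrated error rate of any one size. It should be fixed; it does not invalidate the design.

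**What to change.** Before any unblinded analysis, amend *Outcome assessments and follow-ups* and *Statistical analysis* to state:

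1. One primary visit, for example week 8, the end of training, with the primary contrast being the between-group difference at that visit.
2. One definition of primary step length, for example that of the paretic leg.
3. Step length and gait speed tested with Holm at a family-wise two-sided 0.05: the smaller p-value against 0.025 and, if that succeeds, the other against 0.05.
4. The other visits, the other leg and the secondary outcomes as supportive, reported with estimates and 95% confidence intervals.

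Week 8, the paretic leg and Holm are one workable choice. Requiring both outcomes, one test each, is another, provided that joint power is stated. What matters is that visit, leg and rule are fixed in advance. The gloss on alpha in *Sample size calculation* should then refer to the family-wise rate.

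The cost is wording, plus the notice to the ethics committee and registry that *Trial status and amendments* already foresees. No visit, measurement or participant is added. The statistical price at the first Holm step is a detectable week-8 difference that rises from about 0.75–0.77 to 0.82–0.85 SD if baseline-adjusted, or from about 0.86–0.89 to 0.95–0.98 SD for the change-from-baseline contrast of the planned model.

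### The sample size claims 80% power for a small effect, but f = 0.20 in the test that yields 42 is a between-group gap of roughly 0.8 to 1.1 SD, and 42 matches three measurements, not the planned four

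*Protocol article*

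**What the plan says.** The Sample size calculation section of the protocol article names the test as "F-test, mixed between-within subjects analysis of variance (ANOVA". It sets the type I error rate at 5%, the power at 80% and the correlation between repeated measurements at 0.5, and it assumes an "effect size of 0.20 (small effect size was used as no similar RCT could be found". It concludes: "Based on these assumptions, the total sample size required is 42". Six are then added for 15% dropout, so that "a minimum sample size of 48 participants (24 per group) will be finally required". The section does not say which effect of the ANOVA is powered or how many measurements were entered. It does not translate 0.20 into SD, cm or m/s.

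Outcome assessments and follow-ups fixes four measurements: "All outcomes will be assessed at baseline prior to randomisation, 4, 8 and 20 weeks after the start of intervention". The Abstract gives the same schedule, and the mixed model in Statistical analysis has the same four time levels, with baseline as the reference. That section also defines what will be reported: "Treatment effect will be defined as the adjusted between-group difference and the associated 95% confidence intervals (CI".

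**The concern.** A reader of the sample size section takes away that the trial has 80% power to find a small benefit on step length or gait speed. In a repeated-measures interaction test, however, f is not a standardised mean difference. With two groups it is half the spread of the gap over visits, so a numerically small f can stand for a large difference between arms. The section neither makes this translation nor links the effect size to the between-group difference that will be reported. Without a stated test and measurement count, the 42 also cannot be traced to this trial's design. What is at stake is how the result is read: a non-significant finding from a trial described as powered for small effects invites more confidence in the absence of benefit than the design can give.

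**Working it through.** **Inputs.** From Sample size calculation: alpha 0.05, power 0.80, effect size 0.20 (taken as f, since this is a G-Power F-test), correlation ρ = 0.5, N = 42. From Study design: k = 2 groups, 1:1. From Outcome assessments and follow-ups: m = 4 measurements. My assumption: no nonsphericity correction (ε = 1), which one common correlation with equal variances implies.

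**Step 1: reproduce 42.** For the group-by-time interaction, λ = f²·N·m/(1−ρ), df1 = m−1, df2 = (N−2)(m−1), with N rounded up to an even number.

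| m | N | λ | df | Power |
|---|---|---|---|---|
| 3 | 42 | 0.04·42·3/0.5 = 10.08 | 2, 80 | 0.803 |
| 4 | 36 | 0.04·36·4/0.5 = 11.52 | 3, 102 | 0.807 |
| 4 | 42 | 0.04·42·4/0.5 = 13.44 | 3, 120 | 0.871 |

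Three measurements return 42 exactly; the planned four return 36. The within-subject factor alone gives the same N, but it does not compare the arms. The between-group main effect at f = 0.20 would need 134 (m = 3) or 126 (m = 4), so it cannot be the source of 42.

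**Step 2: what f = 0.20 means.** With two equal groups, f² = v·D²/4, where D is the largest between-group gap in marginal SD units and v is the variance over visits of the gap pattern scaled to a maximum of 1. Hence D = 2f/√v = 0.40/√v.

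| Gap over visits | v | D at f = 0.20 |
|---|---|---|
| 0, D, D | 2/9 | 0.85 SD |
| 0, D, D, D | 3/16 | 0.92 SD |
| linear over four visits | 5/36 | 1.07 SD |
| 0, 0, D, D | 1/4 | 0.80 SD |
| 0, D/2, D, D/2 | 1/8 | 1.13 SD |

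Simulating the interaction F-test for the first three patterns, at the N from Step 1, gave power of 0.807 to 0.808, which confirms the translation.

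**Step 3: power for a between-group difference.** I used a two-sided t-test with n per arm, noncentrality (D/SD)·√(n/2) and 2n−2 degrees of freedom. The documents name no primary time point, so I took two contrasts, both with ρ = 0.5 and equal variances:

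- Change from baseline at one visit: variance 2(1−0.5) = 1, SD 1.
- Mean of the three post-baseline visits minus baseline: variance 1 + (1/3)(1 + 2·0.5) − 2·0.5 = 0.667, SD 0.816.

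| Contrast | Power at 0.2 SD, n = 21 | Power at 0.4 SD, n = 21 | D for 80% power, n = 20 |
|---|---|---|---|
| single-visit change | 10% | 24% | 0.91 SD |
| post-baseline average | 12% | 34% | 0.74 SD |

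**Step 4: dropout.** 15% of 42 is 6.3, which was rounded to 6 and added. To keep 42 after 15% loss needs 42/0.85 = 49.4, so 50. With 48, 48·0.85 = 40.8 remain, and 6/48 = 12.5% is the loss that 48 covers. On the four-measurement requirement, 36/0.85 = 42.4, so 43 (44 for equal arms), which 48 exceeds.

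**The case against.** Several points on the other side stand.

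- A reader might infer that 42 can only come from three measurements. That is too strong. Four measurements also give 42 with a nonsphericity correction of about 0.80, or with alpha 0.025 (power 0.801), for example if alpha were split over the two primary outcomes. The article states alpha 0.05 and mentions no correction, so three is the best reading of its inputs, but it is inferred.
- A reader might infer that the visit mismatch leaves the trial short. It does the opposite: four visits need fewer participants for the same f.
- A reader might take the dropout step as a real shortfall. It is one only against 42. About 40 analysed exceeds 36 and has 85% power for f = 0.20 over four visits, and the mixed model also uses partial data from those who drop out.
- The planned model contains the time-by-treatment interaction, so the powered test is not foreign to the analysis. The article does not say whether the reported difference is per visit or averaged, so week 8 cannot be assumed to be the target. Nor can a baseline-covariate analysis, because baseline is a level of time in the model.
- The SD range depends on an assumed trajectory; the article gives neither a trajectory nor an SD.
- No passage says that a null result would rule out a small effect, and confidence intervals will be reported.

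None of this rescues the label. Every trajectory tried gives at least 0.80 SD, and both contrasts in the working have low power at 0.2 and 0.4 SD.

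**Conclusion.** The power statement is wrong as written. The calculation behind 42 gives 80% power for a gap of roughly 0.8 to 1.1 SD, not for a small effect, and it matches a three-measurement design where the trial has four. The label is the substantive fault. The measurement count is a reproducibility fault that errs on the safe side, and the dropout arithmetic is minor. The conclusion rests on reading 0.20 as f (supported by the exact match at 42), correlation 0.5, equal variances and no nonsphericity correction; the SD figures also rest on the assumed course of the gap.

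A reader might go further and infer that 48 is the wrong number and that the trial must recruit more, perhaps the 126 that a main-effect test would need. The documents do not support that: they set no target difference in SD, cm or m/s against which 48 fails, and the main-effect test is not the one that was used. This should be fixed, but it is a correction to the text and does not change the design.

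**What to change.** Keep 48 and rewrite the Sample size calculation section:

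1. Name the effect tested (the group-by-time interaction, if that is what was run) and the number of measurements, and recompute with four: 36 required, 87% power with 42.
2. Delete the description of 0.20 as a small effect.
3. State the between-group difference detectable with 80% power at two-sided 0.05 and about 40 analysed, as a range under stated assumptions (correlation 0.5, equal variances): about 0.91 SD for a single-visit change from baseline and about 0.74 SD for the average of the three post-baseline visits minus baseline.
4. State that a null result does not exclude a small or moderate effect.
5. Correct the dropout sentence: either say that 48 covers 12.5% loss from 42, or base it on 36, which 48 with 15% loss meets.

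The cost is text only. Recruitment, allocation, outcomes and analysis stay as they are, but the stated power becomes less favourable.
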